### Quality control

All participating staff will attend uniform training before the commencement of the trial to ensure the quality of the trial. The licensed acupuncturists who have a minimum of 2 years’ clinical practice of acupuncture will perform the treatment. Throughout the trial, the principal investigator and a research coordinator will regularly check CRFs, acupuncture operation, patient safety, and data quality. Withdrawals or study dropouts will be clearly described during the trial.

To minimize compliance bias in the topical diclofenac sodium gel group, we will dispense the gel with uniform specifications and provide dosing pads to standardize the applying amount of the diclofenac gel. Diary cards will be also supplied including the exact date and time when using the gel and the dose per use, which are required to be recorded every day by patients. The outcome evaluator will check the returned tubes once the new gel is supplied.

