## Methods and design

### Study design

This will be a parallel-design, assessor-blinded, randomized trial with a 1:1 allocation rate. The study is designed to adhere to the standard protocol items including the Recommendations for Interventional Trials [21] and the Standards for Reporting Interventions in Clinical Trials of Acupuncture [22] guidelines. The study flow diagram and treatment schedule are presented in Figs. 1 and 2.

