### Randomization and blinding

Participants will be randomized to the EA group or topical DSG group at a ratio of 1:1 using a fixed block randomization (block size *n* = 4). The randomization schedule will be generated with PROC PLAN of SAS 9.4 (SAS Institute Inc., Cary, NC, USA) by the study biostatistician. To help conceal the details of the group allocation, consecutively numbered and sealed opaque envelopes prepared by an independent staff member will be used. After the participant has completed all the baseline measurements, the envelopes will be opened in sequence by a research coordinator who will be not involved in treatment and outcome assessments.

The outcome assessor and data manager will be blinded to the group assignments and not involved in providing the interventions. Allocation will be revealed to the researchers (including acupuncturists) delivering the intervention, but participants will be asked to not disclose details about their group allocation with the outcome assessors.

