#### Topical DSG group

Participants will be shown how to apply the topical DSG (Mayinglong Pharmaceutical Group Co., Ltd., Hubei, China; 100 mg of diclofenac sodium per gram of gel, 20 g in each tube; H19990010) under supervision and will be provided with detailed instructions for the use and application of the gel as well as dosing pads to standardize the application amount. The gel will be gently rubbed over the affected joints without excessive joint movement four times per day for 4 weeks, and participants will be asked not to wash their hands for 1 h after application. Each hand treatment will be used in identical dispensing doses of gel (4-cm strip, approximately 2 g, which was judged sufficient for approximately half the surface of each hand [200 cm^2^] [15]). Dosing times should be distributed evenly over waking hours.

If bilateral hands are affected, both sides will be treated. The value in the dominant hand or both hands will be used in the analysis according to the requirements of different outcome measurements.

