The strengths of the trial include the strict inclusion and exclusion criteria, measurement of outcomes recommended by the OMERACT-OARSI, and blinding of the outcome assessor and data manager. We acknowledge several limitations exist in this trial. First, although this study could provide clinically relevant data important for patients with hand OA and the clinicians who treat them, the absence of a comparator group treated with placebo will make it difficult to exclude non-specific physiological responses to acupuncture. Second, we will be not able to blind participants and acupuncturists, which could potentially introduce bias in the results. Third, although symptomatic improvement may occur secondary to structural benefit, we will not use hand imaging assessments, because we do not expect our treatment to bring a structural change in the short term. Fourth, topical DSG will be used four times daily in our study based on evidence from previous literature [15, 41] and clinical experience. However, it may lead to a relatively poor compliance for patients, and result in a certain compliance bias. Fifth, considering the forces acting on the first CMC joint may much higher than that on the DIP and PIP joints in daily life, the comparison of the numbers of joints involved between patients would bring bias; the result will be interpreted as exploratory and viewed with caution. Sixth, the fixed acupuncture regimen will be used in this study; however, whether different acupuncture doses or different acupoints will show different benefits for patients should be evaluated in future studies.

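### The outcome evaluator is assigned to check returned gel tubes, which only the diclofenac arm has; this contradicts the assessor blinding that the protocol claims

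*Protocol article*

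**What the plan says.** The protocol article claims assessor blinding in three places.

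- Study design: "This will be a parallel-design, assessor-blinded, randomized trial with a 1:1 allocation rate".
- Randomization and blinding: "The outcome assessor and data manager will be blinded to the group assignments and not involved in providing the interventions". The safeguard given there against later disclosure is that "participants will be asked to not disclose details about their group allocation with the outcome assessors".
- Discussion, in the list of strengths: "blinding of the outcome assessor and data manager".

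The Quality control section has a paragraph on adherence in one arm, which opens: "To minimize compliance bias in the topical diclofenac sodium gel group, we will dispense the gel with uniform specifications". It goes on to dosing pads and diary cards, and ends: "The outcome evaluator will check the returned tubes once the new gel is supplied".

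The section on the topical DSG group describes the product as "100 mg of diclofenac sodium per gram of gel, 20 g in each tube" and the amount per hand at each application as "4-cm strip, approximately 2 g", used four times a day for 4 weeks. The EA group receives no gel, and the Discussion acknowledges that there is no placebo comparator.

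**The concern.** A blinded assessor should not handle anything that exists in only one arm. Here the protocol's own procedure puts such an object in the evaluator's hands. Asking participants to keep quiet about their group does not help, because the disclosure comes from the tube and not from the participant.

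Participants and acupuncturists cannot be blinded, as the Discussion says. Among the people who take part in generating the outcome data, the assessor is therefore the one whose masking can still limit bias. At stake are the secondary outcomes that depend on how an examiner presses, judges, instructs or encourages: joints painful on digital pressure, swollen joints, grip strength and the three pinch strengths. Also at stake is the accuracy of calling the trial assessor-blinded in its report.

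**Working it through.** The contradiction is one of text, and no figure stated in the protocol is in dispute. The planned size is untouched: a 7-point difference with SD 12, two-sided 5% alpha and 80% power needs 48 per arm by the two-sample t-test. Then 48 / 0.90 = 53.3, rounded up to 54 per arm and 108 in total, as stated.

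**Step 1: the passages side by side.**

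| Question | Answer in the protocol article | Section |
|---|---|---|
| Is the assessor blinded to group? | Yes | Study design; Randomization and blinding; Discussion |
| Who checks returned tubes? | The outcome evaluator | Quality control |
| Which arm has tubes? | DSG only | Topical DSG group; Quality control |
| Is there a dummy gel in the EA arm? | None described | EA group; Discussion |
| Is a second evaluator, separate from the assessor, described? | No | None |

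With two arms, a returned tube identifies DSG. An evaluator who knows that a participant has returned no tubes can infer EA. If evaluator and assessor are one role, the Quality control sentence and the blinding statements cannot both hold.

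**Step 2: is a check likely before the primary time point?** The resupply schedule is not stated, so I use gel consumption as a guide. Inputs, all from the topical DSG section: about 2 g per application per hand, 4 applications a day, 4 weeks (28 days), 20 g per tube.

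- Daily use per hand: 2 g × 4 = 8 g.
- Duration of one tube, one hand: 20 / 8 = 2.5 days.
- Four-week use, one hand: 8 g × 28 = 224 g, and 224 / 20 = 11.2 tubes.
- Four-week use, both hands: 448 g, and 448 / 20 = 22.4 tubes.

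Unless the whole course of 11 to 22 tubes is handed out at once, new gel is supplied during the 4 treatment weeks. The wording of the tube check itself presupposes a later supply. At least one check before the week 4 visit is therefore likely. Knowledge gained then would carry over to weeks 8 and 16. Baseline is safe, because envelopes are opened only after the baseline measurements.

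**Step 3: which outcomes are exposed?**

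- Assessor-measured or assessor-administered: joints painful on pressure, swollen joints, grip strength, and palmar, key and tip pinch strength.
- Reported by participants who know their treatment, or derived from such reports: the primary pain VAS, the 15-point response, AUSCAN, FIHOA, self-reported painful joints, global assessment, OMERACT-OARSI response, WHOQOL-BREF and acetaminophen use. Unblinding the assessor adds little to the bias already possible in these.

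**The case against.** The strongest reply is that evaluator and assessor may be different people. The two terms are used in different sections and neither is defined. This stands as a caveat. Since no other evaluator is described, one role is the natural reading. If there are two, the text needs to say so.

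The second reply is that the consequence is limited. The primary outcome is self-reported by unblinded participants, and the Discussion already names that as a source of bias. The exposed outcomes are secondary. Strength is read from instruments and averaged over three trials, pressure pain still depends on the participant's response, and the Discussion already says that the comparison of numbers of joints involved will be treated as exploratory. All of this stands, and it limits the size of the point. It does not remove the contradiction.

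That the article condenses a fuller protocol is no answer either: the problem is a positive statement that conflicts with others, not a missing detail.

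A reader might also infer more than the documents support:

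- **That all 108 allocations are revealed, through repeated returns by every DSG participant.** Tubes consumed are not return visits. The number of tubes dispensed at a time and the resupply dates are not given. Some participants may leave before any resupply (10% dropout is allowed for). Inferring EA from the absence of tubes requires the evaluator to know who has returned none, and with two hospitals the number of evaluators is not stated.
- **That assessor blinding is the only masking.** The data manager is blinded as well.
- **That the primary result is compromised.** The protocol describes no assessor-rated element in the VAS. Under Rescue medication the assessor postpones a visit after prohibited use, which gives some influence on timing, but under a fixed rule.
- **That the evaluator reviews the diary cards.** No section assigns that task to the evaluator.

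**Conclusion.** The concern holds as a contradiction within the protocol article. If the tube check is carried out as written and the evaluator is the assessor, DSG allocation is disclosed directly, EA allocation can be inferred, and the assessor-blinding claim in three sections is not met for the participants concerned. How many that is cannot be derived from the document. Consumption of one tube per 2.5 days per treated hand makes disclosure before week 4 likely, but does not prove it for each participant.

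The added risk of bias falls mainly on the assessor-measured secondary outcomes. The document gives no basis for putting a figure on it. The sample size and the primary analysis do not change.

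**What to change.** 1. In Quality control, give the return and checking of tubes to the research coordinator who opens the envelopes. That person already knows the allocation and has no part in treatment or outcome assessment. The staff who dispense the gel would serve equally well.
2. In Randomization and blinding, add that the outcome assessor does not see tubes, gel diaries or dispensing records. The mention of diaries is a precaution, since they too exist only in the DSG arm.
3. Use one term for the assessor throughout. If the evaluator is in fact a separate person who assesses no outcomes, say so.
4. If checks have already been done as written, disclose this in the report, qualify the assessor-blinding claim, and interpret the joint examination and strength outcomes accordingly.

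The cost of items 1 to 3 is a sentence or two and one task moved between existing staff, with no added personnel, visits or participants.

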## Discussion

Hand OA is an increasingly prevalent condition among older adults, and it is associated with a serious disease burden [38]. Currently available interventions for hand OA have several limitations, and other analgesic approaches are still needed. Acupuncture has been considered a promising therapy in clinical practice for the management of various pain-related conditions including knee OA [17] with a good safety profile. However, there is a distinct lack of studies assessing the effect of acupuncture for hand OA. Considering the ethics and acceptance by participants, we chose topical DSG, which has been recommended as the preferred treatment option, as an active comparator in this trial. The results of this trial will help determine which of the two treatment protocols, EA or topical DSG, is more effective for the treatment of hand OA in the clinic.

Because measurement of pain is a core outcome domain in hand OA clinical trials [34], and the VAS has been agreed upon as the recommended preliminary instrument for assessing pain [39] with good validity and responsiveness [40], we chose the change in average overall finger joint pain intensity in the dominant hand over the preceding 48 h, measured on a 0–100 mm VAS from baseline to week 4 as the primary clinical endpoint in this study.

Moreover, the outcomes for other core domains (i.e., physical function, joint activity, hand strength, patient global assessment, and health-related QOL) endorsed by OMERACT12 [34] will also be assessed in this trial. The results will provide detailed information regarding the effectiveness of EA as a treatment for hand OA.

The strengths of the trial include the strict inclusion and exclusion criteria, measurement of outcomes recommended by the OMERACT-OARSI, and blinding of the outcome assessor and data manager. We acknowledge several limitations exist in this trial. First, although this study could provide clinically relevant data important for patients with hand OA and the clinicians who treat them, the absence of a comparator group treated with placebo will make it difficult to exclude non-specific physiological responses to acupuncture. Second, we will be not able to blind participants and acupuncturists, which could potentially introduce bias in the results. Third, although symptomatic improvement may occur secondary to structural benefit, we will not use hand imaging assessments, because we do not expect our treatment to bring a structural change in the short term. Fourth, topical DSG will be used four times daily in our study based on evidence from previous literature [15, 41] and clinical experience. However, it may lead to a relatively poor compliance for patients, and result in a certain compliance bias. Fifth, considering the forces acting on the first CMC joint may much higher than that on the DIP and PIP joints in daily life, the comparison of the numbers of joints involved between patients would bring bias; the result will be interpreted as exploratory and viewed with caution. Sixth, the fixed acupuncture regimen will be used in this study; however, whether different acupuncture doses or different acupoints will show different benefits for patients should be evaluated in future studies.

## Data Availability

Data are available upon reasonable request.
